### fNIRS data collection

To investigate the potential mechanisms of Baduanjin training on post-stroke cognitive dysfunction, this study will collect functional near-infrared spectroscopy (fNIRS) data from participants both before and after 12 weeks of intervention. The equipment utilized for this purpose is the Wuhan Zilian Hongkang model BS-3000 fNIRS equipment.Prior to data collection, the study's objectives were thoroughly explained to the participants. They were instructed to keep their heads at rest during the tests and minimize swallowing movements to minimize potential testing errors. The areas sampled include the premotor cortex (PMC), supplementary motor area (SMA), primary motor cortex (M1), and sensorimotor cortex (SMC).The 37-channel fiber optic cap employed in this study comprises 12 light sources and 12 detectors, spaced 3 cm apart in a rectangular grid of 3 rows by 8 columns. Light is emitted from a source and penetrates the scalp and skull, where it is absorbed by oxyhemoglobin and deoxyhemoglobin in the cortex. The remaining light is then detected. Changes in hemoglobin concentration within the region traversed by the channel serve as indicators of local neuronal activity.

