**Discussion:**

This trial aims to examine the impact of Baduanjin training on attentional lateralization among patients with post-stroke cognitive impairment (PSCI). Functional brain imaging utilizing near-infrared spectroscopy will be employed to investigate how Baduanjin exercise influences the structural and functional connectivity of distinct brain regions or brain networks.

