Impaired attention is one of the most common cognitive deficits following a stroke, with approximately 46% to 92% of patients experiencing attentional deficits in the acute phase [6]. These deficits persist in 20% to 50% of cases for several years post-injury [7, 8]. The attentional system comprises three functionally and structurally independent subsystems: vigilance, orienting, and executive control [9].Vigilance refers to the state of heightened sensitivity to external information and its maintenance. Orientation involves the selection of specific information from a vast amount of external input. On the other hand, executive control functions encompass the ability to execute complex behaviors, monitor, and resolve conflicts [10]. These three attentional subsystems are governed and processed by three distinct brain networks: the dorsal attention network (DAN), the ventral attention network (VAN), and the executive control network (ECN). These networks, while relatively independent, work in tandem to complete the attentional process and achieve cognitive control [11]. Our current study suggests that attention processing in the two hemispheres exhibits asymmetry, leading to a biased lateralization of the attentional network. Specifically, there is no significant lateralization for the vigilance function [12, 13]. However, significant left visual field-right hemisphere lateralization is observed for the subnetworks involved in orientation and executive control [14, 15]. Imaging studies have also revealed a strong right lateralization of the VAN in conjunction with the ECN, while the DAN exhibits a symmetrical distribution in both cerebral hemispheres. This implies that the attentional network displays a right-sided lateralization balanced with bilateral coordination, enhancing the efficiency of attentional processes while maintaining bilateral coordination.Nonetheless, it is this right-sided lateralization of attention that leads to the clinical prevalence and severity of left-sided attentional impairments resulting from right brain injuries [16]. Stroke patients experience attentional dysfunction due to damage to the dominant side of the brain region, disrupting the lateralization pattern of the attentional network. Previous studies have demonstrated that right hemispheric infarcts result in an advantage in left hemispheric orienting function processing, while left hemispheric infarcts lead to the loss of this advantage and impair orienting function [17]. Thus, the lateralization pattern of the attentional network in stroke patients is a crucial factor contributing to attentional dysfunction.

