#### Functional connectivity analysis of the attentional network

The degree of signal synchronization in the time domain during the initial 6-min resting phase was assessed using Pearson correlation analysis across all measured brain regions. This analysis provided a connectivity matrix that captured both intra- and interhemispheric connectivity relationships. The elements within the matrix represented the correlation coefficients of the paired channels, with rows and columns corresponding to the channel numbers.Graph Theoretical Analysis was subsequently employed to calculate various node metrics. Nodes with a sparsity greater than 20% were selected for analysis to assess the overall characteristics of the brain network organization. The analysis was conducted using the Graph Theoretical Network Analysis (GRETNA) toolbox. The metrics calculated included global efficiency (reflecting network efficiency), local efficiency (reflecting local network efficiency), and the small-world network property. Higher values of these metrics indicate higher network efficiency and adherence to a small-world network structure.

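### Every cortical area named for fNIRS is motor or sensorimotor, yet the connectivity results are labelled and interpreted as those of the attentional network

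*Protocol article*

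**What the plan says.** The protocol article describes the fNIRS component in several places.

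- **fNIRS data collection**, purpose: "To investigate the potential mechanisms of Baduanjin training on post-stroke cognitive dysfunction, this study will collect functional near-infrared spectroscopy (fNIRS) data", before and after the 12 weeks.
- **fNIRS data collection**, areas: "The areas sampled include the premotor cortex (PMC), supplementary motor area (SMA), primary motor cortex (M1), and sensorimotor cortex (SMC".
- **fNIRS data collection**, hardware: a 37-channel cap that "comprises 12 light sources and 12 detectors, spaced 3 cm apart in a rectangular grid of 3 rows by 8 columns".
- **Connectivity section**: its title is "Functional connectivity analysis of the attentional network". The input is "The degree of signal synchronization in the time domain during the initial 6-min resting phase", which "was assessed using Pearson correlation analysis across all measured brain regions". Global efficiency, local efficiency and the small-world property are then computed.
- **Background** (Introduction): attention is governed by "the dorsal attention network (DAN), the ventral attention network (VAN), and the executive control network (ECN"). VAN and ECN are described as right-lateralized and DAN as symmetrical.
- **Discussion** (main text): an fNIRS-based lateralization analysis is presented as the way to study Baduanjin's effect on lateralization of the attentional network.
- **Abstract, Discussion paragraph**: fNIRS is to "investigate how Baduanjin exercise influences the structural and functional connectivity of distinct brain regions or brain networks". The last paragraph of the Background states the same aim.

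**The concern.** The named areas and the claimed inference do not match. The measured cortex is described only in motor and sensorimotor terms, while the result carries the name of a different system, which the article itself defines.

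This matters more here than it would in a drug trial. The intervention is supervised movement training five times a week. The Background credits Baduanjin with improving motor function after stroke, and the trial measures motor function with the Fugl-Meyer scale. If the metrics differ between groups, a change in sensorimotor organisation is an obvious rival explanation, and the plan has no means of separating it from a change in attention. If the metrics do not differ, the data say little about DAN, VAN or ECN, because no channel is tied to them. Either way, a conclusion about the attentional network would lack support.

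The structural-connectivity aim has a related fault: the article names it as something fNIRS will address but describes no structural measurement.

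**Working it through.** This is mainly a comparison of sections. The only arithmetic concerns the montage.

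**1. Reproduce the channel count.** Inputs from fNIRS data collection: 3 rows, 8 columns, 12 sources, 12 detectors, 3 cm spacing. With sources and detectors alternating, each adjacent pair forms one channel:

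- along rows: 3 × (8 − 1) = 21
- along columns: 8 × (3 − 1) = 16
- total: 21 + 16 = 37

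This agrees with the stated 37 and uses all 24 optodes (12 + 12 = 3 × 8). The stated hardware is therefore one contiguous grid, and no optodes are left over for a second patch elsewhere.

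**2. Extent and matrix size.**

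- Span between outer optodes: (8 − 1) × 3 = 21 cm by (3 − 1) × 3 = 6 cm.
- Channel pairs in the correlation matrix: 37 × 36 / 2 = 666.

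All 666 pairs come from whatever that one band covers. The connectivity section names no channel subset or region of interest that would limit the analysis to attention areas.

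**3. Set the areas beside the networks.**

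| Area named as sampled | Type, by its name | Assigned to DAN, VAN or ECN in the text? |
|---|---|---|
| PMC | motor | no |
| SMA | motor | no |
| M1 | motor | no |
| SMC | sensorimotor | no |

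Four of four are motor or sensorimotor, and none is linked to an attention network.

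**4. Follow the inference.** Fix the nodes as everything measured, take the measured areas as those named, and the three graph metrics describe motor and sensorimotor cortex at rest. The connectivity title and the main Discussion then attribute them to the attentional network and its lateralization. The Background locates lateralization in VAN and ECN, for which no sampled area is named.

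**5. Check what depends on the cap.** MoCA is a rating scale. The attention indices in the section on the lateralization index come from LANT response times and error rates. Neither uses fNIRS, so the mismatch does not reach the primary outcomes.

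**6. Check structural connectivity.** The data-collection, pre-processing and connectivity sections describe haemoglobin signals, GLM coefficients and time-series correlations. All are functional.

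**The case against.** The strongest reply has four parts.

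- **The list may be open.** The text says the sampled areas include these four, and the figures are not available here. This stands as a limit: other areas may be covered. But none is named anywhere, and a channel map showing them would settle the matter.
- **A journal article leaves channel maps to the full protocol.** That would answer a complaint about missing detail. Here the article does state the areas, and the areas it states conflict with its own label and inference.
- **The fNIRS work is already secondary in standing.** Connectivity is not listed as a primary or secondary outcome, the Background introduces it as something additional to explore, and the closing summary promises only initial insight into mechanism. This stands, and it limits the severity.
- **Attention and motor function are measured separately.** LANT, MoCA and Fugl-Meyer results can be read beside the fNIRS results. That helps interpretation, but it does not turn metrics from motor channels into a measure of the attentional network.

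A reader might also infer that the 6 × 21 cm grid cannot cover both motor and attention cortex. The documents do not support this: they give no cap orientation, anchor point, head size or extent of any region, and the Background gives no cortical locations for the three networks. For the same reason, nothing shows that this one grid could simply be moved to cover all the attention regions.

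**Conclusion.** The point holds as a mismatch between the stated areas and the stated inference. As written, the graph metrics come from areas named only as motor or sensorimotor, and they are to be reported as properties of the attentional network. In a movement trial with an expected motor benefit, a group difference in them could not be distinguished from sensorimotor change.

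It is confined to the fNIRS mechanistic aim; MoCA and the LANT-based index are intact. It should be corrected, but it does not threaten the trial's main comparison. No numerical bias can be attached to it.

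The verdict assumes that the four named areas represent the montage and that all measured channels enter the matrix, as the connectivity section says.

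Two stronger readings should be resisted. One is that the mechanistic question cannot be answered at all. The case is strongest for VAN and ECN, and the documents do not exclude some coverage of attention regions. The other is that motor change will be reported as attention change. The article does not say that graph metrics alone will decide this; what is established is that the planned metrics could not separate the two.

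**What to change.** Reconcile the data-collection section, the connectivity section and the main Discussion before scanning, by one of two routes.

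1. **Keep the attentional-network aim.** Confirm, with a channel-to-region map, that the montage covers prespecified DAN, VAN and ECN regions, and restrict the network nodes to those mapped channels. Cost: less motor coverage if the cap has to be re-placed. Feasibility with the single 3 × 8 grid must be checked first and is not established by the text.
2. **Keep the motor placement.** Retitle the connectivity analysis as exploratory sensorimotor connectivity, and remove conclusions about the attentional network or its lateralization that rest on it. Cost: wording only, but the fNIRS data no longer address the attention mechanism.

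The choice needs to come before baseline scans, because cortex not sampled then cannot be recovered later.

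Under either route, delete the word structural from the fNIRS connectivity aims in the Abstract (Discussion paragraph) and the last paragraph of the Background. This costs nothing, since no planned analysis depends on it.

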### Attention to lateralization tests

Attention is a fundamental cognitive function, and the exploration of its characteristics and processes is of paramount importance. The Attention Network Test (ANT) is a valuable tool designed to provide comprehensive scores assessing the efficiency of alerting, orienting, and executive control. In this study, the lateralized attention network test (LANT) was utilized, and the test was conducted using the E-prime 2.0 software.During the LANT, target arrows were presented on a computer screen, with the subject positioned at a distance of approximately 60 cm from the screen. A total of 318 trials were administered, which included 30 practice trials and 288 formal trials, organized into 4 phases. Participants had the opportunity to rest after completing each phase, resulting in a total test duration of approximately 30 min. Assessments were conducted both before the intervention and at the twelfth week of the intervention.

## Intervention

### Conventional treatment group

The foundational treatment was carried out in accordance with the 2017 Expert Consensus on the Management of Cognitive Impairment after Stroke. The specific treatment plans were devised by the attending physicians at the respective hospitals where the patients were receiving care. The personnel involved in this research group did not actively partake in the treatment procedures. Instead, they objectively documented the treatment processes throughout the study duration.Comprehensive records of patients' daily treatment and medication were meticulously maintained during the 12-week intervention period.

### Baduanjin group

In addition to regular treatment, we incorporated Baduanjin training as a supplementary intervention. This training followed the standards outlined in the "Fitness Qigong—Baduanjin" guidelines issued by the State General Administration of Sports in 2003. It consists of ten movements, including the preparatory posture, holding the sky with both hands to manage the three jiao, opening the bow left and right as if shooting an eagle, regulating the spleen and stomach to be lifted single-handedly, looking backward for the five labors and seven injuries, wagging the head and tail to remove the fire in the heart, climbing on the feet with both hands to strengthen the kidney and waist, saving the fist to increase the qi strength of the eyes in anger, eliminating diseases by focusing on the back's seven bumps, and concluding with the closing posture.A trained therapist was present during the training sessions to provide guidance and ensure the safety of participants. The Baduanjin training occurred five times a week, with each session lasting 40 min, and continued for 12 weeks.To eliminate the potential influence of excessive exercise, all participants in both the Baduanjin exercise group and the conventional rehabilitation treatment control group were advised to refrain from engaging in any other forms of exercise during the trial. Their adherence to the Baduanjin exercise methodology was rigorously recorded throughout the study period.

### Assessment of results

The variables considered in this trial encompass basic participant information, primary, and secondary outcomes. Baseline characteristics will be assessed within the window of 1–2 weeks before random assignment.The primary outcomes, namely Overall Cognitive Functioning and Attentional Lateralization Index, will be measured at three time points: pre-intervention, week 6, and week 12 of the intervention.Secondary outcomes will be evaluated both before and after the intervention period. All assessments of primary and secondary outcomes will be conducted by experienced staff at the Shenzhen Bao'an District People's Hospital. These assessors will be blinded to the participants' allocation, ensuring the integrity of the study.

### Basic information

Recruiters will gather comprehensive demographic information from participants, including age, gender, ethnicity, occupation, education level, marital status, past medical history, family medical history, dietary habits, alcohol consumption, frequency of exercise, and more.In addition, prevalence data, such as the duration of stroke and the site of the lesion, as well as the presence of hemiparesis, will also be collected using a self-designed questionnaire. The degree of neurological impairment will be evaluated using the National Institutes of Health Stroke Scale (NIHSS).All baseline measurements will be conducted before participants are randomized into their respective groups.

## Primary outcomes

### Global cognitive function

Global cognitive functioning will be evaluated using the Montreal Cognitive Assessment Scale (MoCA). This scale is widely recognized for its validity and reliability in assessing overall cognition in individuals with mild to moderate stroke [27]. The MoCA assesses various cognitive domains, including attention and concentration, executive functioning, memory, language, visual-spatial skills, abstract thinking, computation, and orientation. Completing the MoCA examination typically takes approximately 10 min. The total score on the MoCA ranges from 0 to 30, with lower scores indicating poorer cognitive function. Additionally, one point is added to the final score for individuals with 12 or fewer years of education.

### Attention to the lateralization index

The study assessed alerting efficiency, localization efficiency, and executive control effects as part of the attentional network effects. These effects were separately calculated for the left and right visual fields.Alerting network effect was determined by subtracting the time (or error rate) of the no-cue response from the time (or error rate) of the dual-cue response.Localization efficiency was calculated by subtracting the time (or error rate) of the dual-cue response from the time (or error rate) of the valid cue response.Executive control effect was derived by subtracting the time (or error rate) of the response in the inconsistent direction of the arrows condition from the time (or error rate).It's important to note that higher values indicated greater vigilance and orientation effects, while lower values indicated stronger executive control effects [12].

### Secondary outcome indicators

#### Rating of cognitive dimensions

Cognitive dimensions will be evaluated using the Mandarin version of the Oxford Cognitive Screening Scale (OCS-P). This scale assesses five cognitive domains, which include memory, verbal cognition, numerical skills, practical abilities, and attentional and executive functions. The OCS-P serves as a valuable assessment tool for the rapid screening of cognitive function in stroke patients, providing guidance for comprehensive cognitive assessments [28].

### Motor function assessment

The Fugl-Meyer Motor Function Assessment Scale (FMA) was employed to evaluate the motor function of the study participants. The FMA is widely regarded as the gold standard for assessing motor function in individuals with hemiplegia following a stroke. This comprehensive assessment encompasses the measurement of voluntary movement, speed, coordination, and reflex activity. As such, it serves as one of the primary components of the secondary outcome measures [29].

### Participation level assessment

The level of participation was assessed using The Pittsburgh Rehabilitation Participation Scale (PRPS), a six-point scale with the following ratings:Score of 1 (none): The patient refused to participate in the entire training or did not engage in any of the exercises within the training.

Score of 2 (poor): The patient refused to participate in at least half of the training or did not take part in at least half of the exercises.Score of 3 (fair): The patient participated in almost all of the exercises but did not exert maximal effort, did not complete most of the exercises, or required significant encouragement.Score of 4 (good): The patient participated to the best of their ability, completing as many exercises as possible but not all, and followed instructions rather than showing intrinsic interest in the exercises and future treatment.Score of 5 (very good): The patient participated in and completed all exercises to the best of their ability but required instruction rather than displaying a strong interest in the training and future treatment.

Score of 6 (excellent): The patient participated in and completed all exercises to the best of their ability and demonstrated a strong interest in the training and future treatment.

The PRPS is recognized for its validity and reliability, providing a quantitative reflection of a patient's rehabilitation participation or initiative. It serves as a credible and practical rehabilitation participation scale [30].

### Activities of Daily Living (ADL)

The assessment of the ability to perform activities of daily living (ADL) will be conducted using the Barthel Index (BI). This standardized scale is widely employed to evaluate functional disability in ADLs. The BI comprises 10 items, and the total score ranges from 0 to 100, with higher scores indicating a better ability to independently manage daily life tasks.The BI is known for its comprehensive, accurate, and efficient assessment of an individual's capacity to carry out activities of daily living [31].

### fNIRS data analysis methods

#### Pre-processing

The data processing steps for functional near-infrared spectroscopy (fNIRS) were as follows:

①The fNIRS data was initially converted from NIRS format to MAT format.②Wavelet-MDL (Minimum Description Length) was employed to remove noise from sources such as heartbeat and breathing.③An HRF (Hemodynamic Response Function) low-pass filter was applied to eliminate signal drift and artifacts.④The necessary parameters for the General Linear Model (GLM) were selected, and β-values were estimated for the model using a t-test with a significance threshold of *P* < 0.05.To account for multiple comparisons, the False Discovery Rate (FDR) correction was utilized. This correction method was employed to output statistical information, including T-values, activation regions, and statistical threshold values.

